### Data processing, analysis and statistics

Results from cerebral Doppler, echocardiography and RH-PAT estimations will be calculated by two independent interpreters blinded to groups and entered manually into the database. MR data will be analysed in collaboration by neuroradiologists, blinded to groups. Blood samples will be thawed for analyses of cardiac, renal, neurological and endothelial biomarkers, analysed through standardised platforms when available and for the remaining through manual ELISA analyses in duplicate. Inter-assay and intra-assay coefficients of variation will be aimed at below 10%.

Demographics will be presented as medians or means as appropriate by distribution and by numbers and percentages as appropriate. Comparison between groups will be analysed by Student’s t-test or Mann-Whitney U-test with means or medians and CIs or IQR, as appropriate according to distribution of the variables. Proportions will be analysed through χ^2^ test. Correlations will be analysed by Pearson’s r or Spearman’s rho as appropriate by distribution of the variable. Regression analyses, unadjusted and adjusted, will be performed to adjust for known confounding variables. Ten cases per variable at the lowest will be considered appropriate to avoid overfitting of the model. All statistical analyses will be performed in SPSS or R. Analyses of cognitive function will be performed through analysis of variance and multivariate analysis of variance.

Data analysis of the interview data will be conducted by phenomenology with a lifeworld approach^36^ or with qualitative content analysis.^37^ NVivo V.10 software (qsrinternational.com/) is used for grouping and organising the text.

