### Aims

The overall aim of this study is to establish a database and biobank including two Swedish University pre-eclampsia cohorts: GO PROVE (Gothenburg Preeclampsia Obstetric adverse events) and UP MOST (Uppsala Pregnancy Complication Study) for pre-eclampsia research, to facilitate laboratory-based, translational and clinical research on pre-eclampsia and to contribute to a safer and more patient-centred care of women with pre-eclampsia in the acute and long-term perspective, focused on specific organ involvement. Thus, the following actions are included in the project:

To establish a biobank and database with core predictors and outcomes for pre-eclampsia research in Sweden (GO PROVE and UP MOST).To examine alterations in cerebral structure and function through magnetic resonance (MR) investigation of the brain, Doppler examination of cerebral blood flow, cerebral biomarkers, electroencephalograms (EEG) and neurocognitive assessment of mental processing speed, working memory, executive functions and episodic memory in women with pre-eclampsia compared with normotensive controls at diagnosis and at 1 year post partum (GO PROVE and UP MOST).To examine cardiac impairment and prediction of cardiac impairment through echocardiography and cardiac biomarkers in women with pre-eclampsia compared with normotensive controls at diagnosis and at 1 year post partum (GO PROVE).To examine vascular dysfunction through measurement of peripheral resistance and blood-based endothelial biomarkers in women with pre-eclampsia compared with normotensive controls at diagnosis and at 1 year post partum (GO PROVE).To examine coagulation profiles through blood-based biomarkers and tests such as thromboelastometry (ROTEM) and impedance aggregometry (Multiplate) in women with pre-eclampsia compared with normotensive controls (GO PROVE)To increase the knowledge and understanding of women’s and their partners’ experiences of pre-eclampsia during pregnancy, birth and post partum through validated measurements and qualitative interviews (GO PROVE).

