#### Exclusion criteria

Women unable to understand oral and written information and unable to give written informed consent are not eligible as well as women with pre-existing hypertension, diabetes mellitus before or during pregnancy and pre-existing cardiovascular, renal or cerebral disease. MR contraindications for MR group includes claustrophobia. Women who have previously been included in the study will not be eligible for their next pregnancy.

For the database and biobank as a whole, there will be no matching. For specific substudies, there might be matching on a group level for gestational age at examination.

The diagnosis of pre-eclampsia will be established according to Swedish guidelines for hypertensive disorders in pregnancy (www.sfog.se) that generally follows international guidelines such as the international society for the study of hypertension in pregnancy (ISSHP), the National Institute for Clinical Excellence (NICE) and the American College of Obstetricians and Gynecologists (ACOG) with the addition that we will require proteinuria to be present to limit the heterogeneity of the population.

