#### Neurocognitive assessment

To determine whether the participating women experience cognitive impairment, several instruments that measure, both subjective and objective cognition, provide a fine-grained picture of the participants’ cognitive performance. Subjective cognitive function is assessed by the Cognitive Failure Questionnaire (CFQ) measuring self‐reported cognitive failures in everyday life.^14^ The objective cognitive test battery consists of 11 tests covering a broad range of cognitive abilities. Verbal ability is assessed with a Swedish four-alternative multiple-choice synonym test (SRB 1) and serves as an estimate of premorbid cognitive ability.^15^ Mental speed is measured by Digit Symbol Coding from Wechsler Adult Intelligence Scale (WAIS IV).^16^ Working memory is assessed by the letter-number sequencing task and the three-digit span tasks forward, backward and sequencing from WAIS-IV.^16^ Executive functions are measured by three tasks from the Delis–Kaplan Executive Function System (D-KEFS): (1) mental shifting/flexibility with the Trail Making Test; (2) inhibition with the Stroop test; and (3) verbal fluency with Letter and Category fluency test.^17^ Several aspects of episodic memory performance are measured with free and delayed recall of nouns using the Buschke Selective Reminding procedure and prospective episodic memory with the Reminding task.^18 19^ All cognitive tests have good psychometric properties. The tests are administered by study personnel, at inclusion at the hospital and again at 1 year post partum.

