### Power calculations

Uppsala and Sahlgrenska University hospitals have 4200 and 10 500 deliveries yearly respectively and Södra Älvsborgs Hospital 3100 deliveries yearly. Pre-eclampsia affects 3% of the population resulting in approximately 530 cases yearly at the centres and approximately 410 cases after exclusions according to the study protocol. For logistical reasons, all women cannot be included. Of eligible, we estimate that we will recruit around 20% for MR, transcranial Doppler and cognition examinations (70/year) at Uppsala and Sahlgrenska University hospitals and about 40/year at Sahlgrenska University hospital for cardiac and endothelial function tests. Therefore, we estimate that inclusion will take 2 years. Inclusion during 2 years at two centres will thus give around 140 MR investigations, 100 transcranial Doppler and cognition examinations and 40 TTE. We will include 60 controls for each investigation. For blood-based tests, we will use the whole cohort. We want to include more cases than controls since we want to be able to subtype cases based on pre-eclampsia phenotypes. Some specific power calculations:

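### The method named for cognition has no covariate and gives the premorbid-ability test (SRB 1) no stated role, so the case-control contrast may carry prior differences and gives up precision

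*Protocol article*

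**What the plan says.** The section on data processing, analysis and statistics first sets out general methods: two-sample tests, chi-squared tests and correlations. It then says: "Regression analyses, unadjusted and adjusted, will be performed to adjust for known confounding variables". The confounders are not listed, and the sentence is neither tied to nor withheld from any outcome. The section ends its quantitative part with a rule for one domain: "Analyses of cognitive function will be performed through analysis of variance and multivariate analysis of variance".

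The neurocognitive assessment section describes an objective battery of 11 tests. SRB 1 covers verbal ability and "serves as an estimate of premorbid cognitive ability". On timing it says: "The tests are administered by study personnel, at inclusion at the hospital and again at 1 year post partum".

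On comparability of the groups, the exclusion criteria section says "For the database and biobank as a whole, there will be no matching" and adds: "For specific substudies, there might be matching on a group level for gestational age at examination". The power section expects "100 transcranial Doppler and cognition examinations and 40 TTE" over two years, and 60 controls for each investigation.

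**The concern.** The stated purpose of the battery is to find out whether the women have cognitive impairment, which implies a comparison with an earlier level. No score from before the disease exists, because testing starts at inclusion, after diagnosis. SRB 1 is the only stated stand-in for that level, yet the analysis text does not use it.

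The design does not fill the gap. The only matching mentioned is possible group-level matching on gestational age, which does not balance ability, age or education. Controls are healthy volunteers, and only about 20% of eligible cases are expected to join this part of the study. A difference in prior ability between the groups is therefore possible, and a plain ANOVA or MANOVA would not separate it from a difference due to pre-eclampsia.

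Precision is also at stake. A covariate that correlates with the outcomes reduces residual variance whether or not the groups differ on it.

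**Working it through.** **The plan's own figures.** The article gives no effect size, SD or power for cognition, so there is no such calculation to reproduce. The nearby recruitment figure does reproduce: (10,500 + 4,200) × 0.03 × (410/530) × 0.20 = 68 per year, against 70 stated.

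**Inputs.** From the power section: 100 cognition examinations, read as cases, and 60 controls. Assumed, because the documents give no values: two-sided alpha 0.05, 80% power, outcome SD 1, a case-control gap g in premorbid ability (in SD), a correlation r between SRB 1 and the outcome, and no true effect of pre-eclampsia.

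**Standard error and detectable difference, unadjusted.**
- SE = √(1/100 + 1/60) = 0.163 SD
- Detectable difference = (1.96 + 0.84) × 0.163 = 0.46 SD

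**Bias without the covariate.** Bias = g × r. With g = 0.3 and r = 0.5 this is 0.15 SD.

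**False-positive rate per test.** Φ(bias/SE − 1.96) + Φ(−bias/SE − 1.96). With bias/SE = 0.15/0.163 = 0.92, this is 0.149 + 0.002 = 0.151, about 15%. A 4,000-run simulation of the same case gave 15.5% without the covariate and 5.5% with it. The simulation treats SRB 1 as an exact measure of premorbid ability, so the return to about 5% is a best case.

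**Range.**

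| Gap g | r | Bias (SD) | False-positive rate, unadjusted |
|---|---|---|---|
| 0 | any | 0 | 5% |
| 0.1 | 0.3 | 0.03 | 5% |
| 0.3 | 0.5 | 0.15 | 15% |
| 0.5 | 0.5 | 0.25 | 33% |
| 0.5 | 0.7 | 0.35 | 57% |

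**Precision.** Adjustment multiplies the SE by about √(1 − r²). The detectable difference of 0.46 SD becomes 0.44 at r = 0.3, 0.46 × 0.866 = 0.40 at r = 0.5, and 0.33 at r = 0.7. Put as sample size, 100 against 60 is worth 2/(1/100 + 1/60) = 75 per group. At r = 0.5 adjustment is worth a factor 1/(1 − 0.25) = 1.33, so about 100 per group. This gain does not need any imbalance.

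**Is SRB 1 an outcome?** Counting the tests named in the neurocognitive section: SRB 1 (1), Digit Symbol Coding (1), letter-number sequencing (1), digit span (3), D-KEFS tasks (3), the Buschke procedure (1) and the Reminding task (1) make 11. On this count SRB 1 is one of the 11. The aims, however, list processing speed, working memory, executive functions and episodic memory, and not verbal ability. The text does not settle whether SRB 1 enters the MANOVA.

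**The case against.** The strongest objection is that silence is being read as exclusion. The general sentence on adjusted regression is not limited by outcome, nothing says that cognition is exempt, and a condensed article commonly leaves covariate lists to the full protocol or analysis plan. ANOVA and MANOVA may be named only because there are many tests and because cases are to be subtyped into more than two groups. This stands in part: the documents do not show that SRB 1 will be left out. But cognition is the only quantitative domain given its own method, and that method comes after the general sentence. A reader cannot tell whether the adjustment carries over.

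Second, a stable prior difference largely cancels in within-woman change from inclusion to one year. That is correct for change. It does not help the case-control contrasts at diagnosis and at one year, which the aims also call for.

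Third, the size of the bias rests wholly on an assumed gap and correlation, and the exclusion of prior hypertension, diabetes and cardiovascular, renal or cerebral disease removes some sources of prior difference. This stands.

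A reader might go further and infer that prior differences will be reported as an effect of pre-eclampsia, or that SRB 1 is certain to be a MANOVA outcome. The documents support neither. No sentence attributes an unadjusted gap to the disease, and the discussion is cautious about causality. The place of SRB 1 in the outcome vector is an inference from the test count, and the list of cognitive domains in the aims points the other way.

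**Conclusion.** The point holds as a gap in the stated method that can be closed at almost no cost. It is not a proven analysis error. The one method named for cognition has no covariate, the role of SRB 1 is unstated, and no matching covers ability, age or education. For 100 cases and 60 controls, an assumed gap of 0.3 SD with r = 0.5 gives a bias of 0.15 SD and about a 15% false-positive rate per test. Over assumed gaps of 0.1 to 0.5 SD and correlations of 0.3 to 0.7, the bias runs from 0.03 to 0.35 SD and the rate from 5% to 57%. With no gap the bias is zero. The precision gain depends only on the assumed correlation, and at r = 0.5 the detectable difference falls from about 0.46 to 0.40 SD.

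**What to change.** State that case-control comparisons of cognition use ANCOVA/MANCOVA, or the regression equivalent, with group as factor and SRB 1 and age as covariates, plus education where recorded. Report the unadjusted contrast as a sensitivity analysis. State that SRB 1 is a covariate and is not part of the MANOVA outcome vector.

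The cost is wording and two or three degrees of freedom. SRB 1 is already collected, and with about 100 cases the plan's own limit of ten cases per variable allows 100/10 = 10 variables, well above group plus three covariates. One limit should be stated with the result: SRB 1 is itself measured after diagnosis, so it is a proxy, and adjustment reduces confounding by prior ability without fully removing it.

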### Power calculations

Uppsala and Sahlgrenska University hospitals have 4200 and 10 500 deliveries yearly respectively and Södra Älvsborgs Hospital 3100 deliveries yearly. Pre-eclampsia affects 3% of the population resulting in approximately 530 cases yearly at the centres and approximately 410 cases after exclusions according to the study protocol. For logistical reasons, all women cannot be included. Of eligible, we estimate that we will recruit around 20% for MR, transcranial Doppler and cognition examinations (70/year) at Uppsala and Sahlgrenska University hospitals and about 40/year at Sahlgrenska University hospital for cardiac and endothelial function tests. Therefore, we estimate that inclusion will take 2 years. Inclusion during 2 years at two centres will thus give around 140 MR investigations, 100 transcranial Doppler and cognition examinations and 40 TTE. We will include 60 controls for each investigation. For blood-based tests, we will use the whole cohort. We want to include more cases than controls since we want to be able to subtype cases based on pre-eclampsia phenotypes. Some specific power calculations:

#### Cerebral blood flow regulation and tissue perfusion

In order to demonstrate a change of 3 mL/min×100 g in perfusion in the cortical subvolume of the brain,^38^ 44 cases of pre-eclampsia and 44 normotensive controls with healthy pregnancies are required. In order to detect a difference in dynamic cerebral autoregulation index of 1.2,^20^ a sample size of 32 women in each group is estimated to be required. In addition, differences in cerebral perfusion and dynamic cerebral autoregulation have been detected in the above sample sizes of 44 and 20 pre-eclampsia cases, respectively, with an equal number of normotensive controls.

#### Cognition

In a meta-analysis, a difference in the objective test ‘letter number sequencing task’ was found when pooling results from 101 women with previous pre-eclampsia and 98 women with previous healthy pregnancies.^39^

### Patient and public involvement

To ensure that the research is relevant, acceptable and feasible from the women’s and partners’ point of view, patient representatives were invited to participate in the research process.^40^ Focusing on women’s and their partners’ experiences of pre-eclampsia diagnosis and care at the same time will ensure that findings from this project will improve not only clinical outcome measures but also women’s and their partners’ experience.

### Ethics and dissemination

This is a cohort study with a control group with no intervention for the participants. Incidental pathological findings on examinations performed are and will be handled in accordance with clinical routine. Data are stored in a secure online database. Biobank samples are identified through the women’s personal identification number and pseudonymised after identification in the biobank before analysis. Results from the study will be published in international peer-reviewed journals.

## Discussion

There is a need for more individualised treatment of women with pre-eclampsia with respect to different organ manifestations of the disease. This in order to individualise treatment and care, such as an informed decision to deliver and to avoid short-term and long-term complications for the mother and infant. Currently, there are no reliable methods in clinical practice to evaluate organ dysfunction such as cardiovascular and cerebral effects of pre-eclampsia, although cerebral oedema, intracranial bleeding and pulmonary oedema, potentially secondary to heart failure are the most common causes of maternal mortality due to pre-eclampsia. There are emerging biomarkers and prediction models but none of them are used in routine care yet and they do not seem to be able to differentiate between different organ dysfunctions.^41 42^

The interdisciplinary team of obstetricians, midwives, anaesthesiologists, neuroradiologists and cardiologists enables us to link organ specialists in the field of pre-eclampsia research. This collaboration will enable important discoveries that have great potential to improve the care of these women. In addition, by employing a database created to harmonise data collection in pre-eclampsia research, biological samples and data can be shared with other research groups, enabling larger datasets for rare outcomes.^7^ Prospective recruitment may imply selection bias. In this study, inclusions will mainly occur daytime by research personnel even though medical staff have the opportunity to include women after office hours (between 16:00 and 08:00). This might introduce selection bias regarding severity of disease where women with sudden onset of organ complications are more often seen and delivered after office hours. In addition, there might be a larger proportion of women with early onset pre-eclampsia recruited since women with late onset pre-eclampsia are induced shortly after diagnosis. However, national health records are available to compare demographics of the study population to the general population with pre-eclampsia.

Regarding cerebral dysfunction in pre-eclampsia, we will be able to further characterise imaging abnormalities, circulating cerebral biomarkers and cognitive function among women with pre-eclampsia and neurological impairment. Some women with pre-eclampsia show evidence of cerebral oedema in the acute phase^43 44^ and long-term follow-up of women with previous pre-eclampsia demonstrate an increased number of white matter lesions.^45^ There is a paucity in data regarding the connection between acute lesions and long-term effects on the brain and their implications in the development of stroke, epilepsy and dementia. Cerebral biomarkers have been reported to be increased in pre-eclampsia but the connection to objective findings on MR or cognitive function is not clear.^46 47^ Hopefully, data from this study can enable an objective assessment of neurological function in pre-eclampsia as a tool for targeting women at risk for adverse cerebral events. In addition, the long-term cerebral effects of pre-eclampsia are still an area that needs more research. There are reports of an increased risk of dementia, stroke and epilepsy after a pregnancy complicated by pre-eclampsia but the causality and importance of pre-eclampsia as an insult to the brain is not fully elucidated.^48–50^ Cognitive impairment years after a pregnancy complicated by pre-eclampsia has been reported but it is not known whether this cognitive impairment exists already at diagnosis and how it changes over the first year post partum after pre-eclampsia.^51 52^ Findings from this study might increase the understanding of the underlying pathophysiological mechanisms of acute cerebral injury and long-term effects.

Regarding haemostasis, our results will hopefully provide guidance as to when women with pre-eclampsia can receive spinal anaesthesia and further insight into the coagulation profile among women with severe pre-eclampsia.

For pre-eclampsia and cardiovascular function, an initial assessment of cardiovascular function with TTE and peripheral resistance measurement for assessment of endothelial dysfunction for all women in the study will aid in the risk-classification of women stratified on cardiovascular involvement.

Increased knowledge about how women as well as partners experience pre-eclampsia and the consequences could improve personalised care and follow-up after pre-eclampsia.

Pre-eclampsia is a disease only manifested in humans, hence there are no animal models of pre-eclampsia with the ability to exactly mimic the true pre-eclampsia state.^53^ Therefore, it is imperative that critical laboratory and clinical observations are made on humans and human tissues. By creating a database and biobank, we will be able to make important laboratory discoveries that can be translated to clinical trials that may improve the care of women.
